### Time plan of the RCT

The enrollment of PHCCs took place from May 2015 to November 2015. The intervention took place between May 2015 and January 2016. Follow-up of sickness absence, healthcare measures and prescribed medications in the registers will be completed one year after last inclusion, i.e. January 2017. Short-term sick leave is followed-up by telephone or e-mail at 3, 6, and 12 months until January 2017.

### Process evaluation, design and procedure

Both qualitative and quantitative methods were used in the process evaluation. The target group of the process evaluation consisted of the intervention GPs. The GPs’ considerations on management before, during and after intervention were assessed by questionnaires. Prior to the brief training, the GPs answered questions on readiness to use the WSQ in patient–GP consultation. Directly after each patient–GP consultation, the GP answered questions on adherence to the study protocol. After data collection, the GP answered questions on the feasibility of using the WSQ in patient–GP consultation in daily practice in the future.

After the baseline data collection was completed at each PHCC, all intervention GPs at that particular PHCC were invited to focus group discussions that explored the GPs’ perception of the systematic use of the WSQ. Oral and written information was given and informed consent for the focus group study was provided. The group sessions were held at the PHCC and were moderated by a researcher experienced in focus group methodology. The discussions focused on the following key questions: views on the content of the intervention, how to improve the process, views on the readiness to use the WSQ combined with feedback in daily practice, and how to facilitate future implementation and permanent use of the WSQ at the PHCCs. The group sessions were audio taped, transcribed verbatim and analyzed according to the method of Krueger [38].

### Allocation and baseline characteristics

In total, 66 GPs were randomized to either the intervention group or to the control group. One GP declined participation and two GPs were excluded because of not having the target group at consultation. The intervention group (systematic use of the WSQ and feedback during patient–GP-consulting) consisted of *n* = 29 GPs and the control group (TAU) of *n* = 34 GPs (Fig. 2).

**Fig. 2 Fig2:**
[figure not shown]
Flow chart of enrolment, allocation and baseline, TIDAS in New Ways

During the inclusion period, 301 non-sick-listed employed women and men aged 18 to 64 years who sought care at the seven participating PHCCs in the Västra Götaland region and fulfilled the inclusion criteria were asked to participate in the study. Of these, 20 eligible patients (7%) declined to participate. A total of 10 patients (3%) were excluded because they left the PHCC before being asked to fill in the questionnaires. No statistically significant differences in responses by participant age or gender were found. The final study population consisted of 271 participants (Fig. 2), of which 132 belonged to the intervention group and 139 to the control group.

The mean age was 46 years (standard deviation = 12) in the intervention group and 43 years (standard deviation = 11) in the control group, with a larger proportion in the age group 51–64 among intervention participants. Also, a larger proportion in the intervention group was consulting the PHCC for musculoskeletal reasons. Otherwise, there were no statistically significant differences between the groups in terms of baseline characteristics concerning sociodemographic factors and reasons for consulting the PHCC (Table 1).

**Table 1 Tab1:** Characteristics of participants in the intervention and control groups, *n* = 271, TIDAS in New Ways

	Intervention *n* = 132	Control *n* = 139
	n^a^ (%)	n^a^ (%)
Gender		
Female	88 (67)	97 (70)
Age categories		
19–30 years	21 (16)	26 (19)
31–50 years	58 (44)	76 (54)
51–64 years	53 (40)	37 (27)^c^
Birthplace		
Nordic countries	122 (93)	125 (90)
Other	9 (7)	14 (10)
Educational level		
Compulsory schooling	13 (10)	15 (11)
Secondary school	61 (46)	59 (42)
University or higher	57 (44)	65 (47)
Occupational class		
Skilled/unskilled manual	49 (37)	58 (42)
Medium/low non-manual	60 (46)	56 (41)
High-level non-manual	23 (17)	24 (17)
Employer		
Private	61 (46)	68 (49)
Public	66 (50)	61 (44)
Self-employed	5 (4)	9 (7)
Reason for consultation^b^		
Mental or behavioral	75 (57)	69 (50)
Musculoskeletal	62 (47)	44 (32)^c^
Gastrointestinal	26 (20)	28 (20)
Cardiovascular	16 (12)	16 (16)
Other	29 (22)	27 (19)

^a^Dispersed numbers of participants are owing to internal

missing data

^b^Multiple responses were optional

^c^Statistically significant differences (tested with the 95% CI for difference in proportion)

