### Masking (blinding)

Neither participants nor the GP were blinded to allocation in the RCT because of the nature of the intervention. All participants were given information on the study and signed consent forms before the patient–GP consultations. However, the control GPs were not informed when a patient for consultation was a study participant, and the controls filled in the questionnaires after consultation.

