### Control group

Control participants received TAU, i.e. an ordinary patient–GP consultation. The GP had no information on whether the patient was a study participant. After the GP consultation, the participant completed the WSQ and answered questions on background characteristics (Fig. 1).

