### Statistical analysis

The analyses will follow the intention-to-treat principle [37]. Per protocol analyses will be conducted to examine if deviations from the protocol have caused bias. Both descriptive and analytic statistics will be used to compare the intervention group and the control group. Analysis will be adjusted for gender and other possible confounders. Sub-group analyses will be done with regard to gender, and if possible given the number of participants, age and diagnostic groups. Non-parametric statistics will be used when ordinal data are analyzed. Otherwise, parametric statistics will be used [37].

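### Ten approached patients were dropped for lack of a baseline questionnaire, probably mostly controls; any of them who had signed consent belong in the intention-to-treat analysis

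*Protocol article*

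**What the plan says.** Under Allocation and baseline characteristics, the protocol article gives the patient flow. It says that 301 patients who "fulfilled the inclusion criteria were asked to participate in the study". Next come the refusals: "Of these, 20 eligible patients (7%) declined to participate". A separate group follows: "A total of 10 patients (3%) were excluded because they left the PHCC before being asked to fill in the questionnaires". Then: "The final study population consisted of 271 participants", of which "132 belonged to the intervention group and 139 to the control group". Responses are said not to differ significantly by age or gender; no comparison by arm is given.

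Five other sections bear on these ten patients:

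- **Masking (blinding):** "All participants were given information on the study and signed consent forms", and this is placed before the consultation for both arms.
- **Data collection:** the consent asked for covers linkage to registers during follow-up.
- **Intervention group and Control group:** intervention patients complete the questionnaires before seeing the GP. For controls the order is reversed: "After the GP consultation, the participant completed the WSQ and answered questions on background characteristics".
- **Primary outcome:** sick leave days and absence periods over 12 months come from the social insurance register.
- **Statistical analysis:** "The analyses will follow the intention-to-treat principle".

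**The concern.** The stated reason for removing the ten is a missing questionnaire, not a refusal and not ineligibility. The questionnaire is not needed for the primary outcome. A patient who had consented and then went home without completing it would still have a register outcome, in an arm already fixed by which GP they saw.

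The condition for staying in the study also differs by arm. A control had to remain at the centre after the visit was over. An intervention patient was given the forms while waiting for the visit they had come for. Slipping away before the forms is easy in the first case and less natural in the second. Among controls, leaving promptly could also be related to how the consultation went.

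At stake is a possible exclusion after GP allocation that differs between arms. It could bias the primary comparison in either direction, in a plan that commits itself to intention-to-treat.

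**Working it through.** **Inputs.** From Allocation and baseline characteristics: 301 asked, 20 declined, 10 removed, 132 intervention and 139 control patients retained. From Sample size: a target difference of 15% in registered days. The arm split of the ten and their sick leave are not in the text, so both are varied below as assumptions.

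**Reproducing the article's flow.**
- 301 - 20 - 10 = 271, and 132 + 139 = 271. The flow closes exactly, so the ten are not among the decliners.
- 20/301 = 6.6% (stated 7%) and 10/301 = 3.3% (stated 3%). Both agree.
- With the ten restored, 271 + 10 = 281, and 10/281 = 3.6%.

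**Exclusion rate by arm.** If *c* of the ten were controls, the control rate is c/(139 + c) and the intervention rate is (10 - c)/(132 + 10 - c).

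| Controls / intervention among the ten | Control arm | Intervention arm | Fisher exact p |
|---|---|---|---|
| 10 / 0 | 10/149 = 6.7% | 0/132 = 0% | 0.002 |
| 8 / 2 | 8/147 = 5.4% | 2/134 = 1.5% | 0.11 |
| 5 / 5 | 5/144 = 3.5% | 5/137 = 3.6% | 1.0 |

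The differential loss depends entirely on a split that the text does not give.

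**Effect on mean days if all ten were controls.** Let the mean days of the ten be *k* times the mean of the retained 139 controls. The full control mean, relative to the retained mean, is (139 + 10k)/149.
- k = 0: 139/149 = 0.933, a change of -6.7%.
- k = 1: 149/149 = 1, no change.
- k = 2: 159/149 = 1.067, a change of +6.7%.

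**Against the target.** Read the 15% as a relative reduction in mean days (an assumption), and suppose the 271 show an intervention-to-control ratio of 0.85. Restoring the ten would give 0.85 × 149/139 = 0.911, an 8.9% reduction, if k = 0. It would give 0.85 × 149/159 = 0.797, a 20.3% reduction, if k = 2. The multiples of *k* show how far the result could move; they are not an estimate of the bias.

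**The case against.** The strongest reply is that the ten may never have been enrolled. The consent sentence under Masking (blinding) speaks of participants, and the 271 participants do not include the ten. The Discussion mentions patients who declined and patients who were excluded from participation together, then says that certain data on non-participating patients were not collected for ethical reasons. On that reading the ten were approached but did not sign. Intention-to-treat is then not breached, and the consent described gives no basis for linking their records. GPs, not patients, were randomised, so a loss at that stage is a recruitment problem in a cluster design. The article also discloses the number and the reason, and it need not define the analysis set in full.

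Most of this stands as a limit on the claim. A reader might infer that all ten were consented controls and that intention-to-treat has therefore been broken. The documents do not support that. No split is given in the text, and the flow chart (Fig. 2), which is not available here, may contain one. An intervention patient could also have been missed, since the forms took about 15 minutes before the visit and someone could leave, or be called in, before receiving them. Signed consent is an inference from the described sequence, not a statement about these ten. Nor can the effect be put as a change in the proportion absent without a rate that the article does not give; the outcome is a number of days.

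What the reply does not remove is the asymmetry in the written procedure, which holds whatever Fig. 2 shows. The reassurance on age and gender does not address it. Nothing in the article rules out that some of the ten had signed.

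**Conclusion.** The point holds in conditional form. Ten patients who did not decline were removed for want of a questionnaire that the primary outcome does not require. The order of procedures makes it probable that most were controls. For each of the ten who had signed consent, removal is inconsistent with the stated analysis principle; for any who had not, it is proper.

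The size is modest but not negligible: 3.6% of 281 overall, and at most 6.7% of the control arm. The direction and amount of any bias in mean days are unknown. The ±6.7% change in the control mean rests on all ten being controls and on assumed multiples of zero and two. At an even split the arms lose equal shares and the differential element disappears.

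This should be resolved before the register analysis.

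**What to change.** 1. Check the consent forms of the ten.
2. Include those with signed consent in the primary register-based analysis, in the arm of the GP they saw. Either impute their missing questionnaire covariates or limit adjustment to age and sex. The article's comparison of responses by age and gender suggests that these two were recorded.
3. Keep the 271 as a sensitivity analysis.
4. Report the ten by arm and consent status. If Fig. 2 already gives the arm, only consent status needs adding.
5. If none had signed, say so, describe the 271 as the enrolled set, and name possible differential loss at recruitment as a limitation.

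The cost is a check of at most ten forms, up to ten more identifiers in the register request, and one extra analysis. The article says that follow-up data were still to be collected, with register data due in January 2017, so the change was feasible at that stage.

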## Discussion

There is a high level of sickness absence in Sweden, and stress-inducing factors at work play a large part in the sickness absence rate. Major efforts have been made to reduce sickness absence by restricting the sickness insurance scheme, by introducing monetary incentives to health care providers, and by specific recommended interventions, such as multimodal intervention and behavioral therapy [39]. However, none of these measures had long-term effects [39, 40]. Preventing and reducing sickness absence is challenging, and new measures are needed. Prolonged exposure to adverse psychosocial work conditions can cause stress, which in turn can lead to poor health. This scenario constitutes an obvious risk for people to be sick-listed [41–43]. People turn to their PHCCs to get help. The GPs, though, report little knowledge of work-related factors [21, 24], and rarely talk to their patients about organizational and psychosocial work-related factors [26, 27]. It is, however, essential to identify the patient at risk of being sick-listed at an early stage. This enables the GPs to take appropriate measures preventing health problems and subsequent sick leave. To date, no method exists that can be used in primary health care to identify people at risk for sick-listing due to work-related stress.

Up to now, many interventions have focused on treatment and rehabilitation of individuals already on sick leave. This is very important, but preventing sick leave is better still. Once a person is sick-listed, the return-to-work process is very costly, and this shows that much is to be gained from early identification. The focus of this project very much corresponds to needs expressed by individuals as well as society as a whole. This study is expected to show if early identification of work-related stress, using the WSQ, combined with feedback at consultation, can serve as a method for health care professionals in PHCCs to prevent or reduce sickness absence over a 12-month follow-up.

Fortunately, we reached our target sample size for participating patients. Also, the fact that few sociodemographic differences were identified between the groups was an advantage. The intervention participants were somewhat older and had a higher rate of musculoskeletal complaints as reasons for consultation. The rates of patients declining and being excluded from participation were low, and no differences concerning gender and age were observed. A limitation is that we did not collect data on non-participation patients’ reasons for consultation or reasons to decline participation because of ethical considerations.

The advantages of randomizing at the GP level were considered as twofold: the risk for variations in sociodemographic and socioeconomic factors between participating patients in intervention and controls were reduced, and engaging the whole PHCC to recruit both to intervention and control groups led to more participants attending in earlier studies [44]. The disadvantage of randomizing at the GP level was the risk for contamination, because the GPs might discuss the study procedure with each other. Because the inclusion period was short, and the intervention was brief and imbedded in ordinary daily practice, the contamination risk was considered rather low.

A strength of this project is that both qualitative and quantitative methods were used in the process evaluation. The focus group methodology involves group discussions and is distinguished from other qualitative group interviews by the explicit use of group interaction to collect data on a specific research topic. Communication between the participating focus group members is decisive for the outcome and the group process encourages the participants to clarify not only what they think, but also how and why they think in a certain way [38, 45]. An experienced group leader was chosen to moderate the sessions because the role of the group leader is essential in creating an open and friendly atmosphere that makes participants feel free to express their views [45]. In addition to using the questionnaires on GPs’ readiness and feasibility in the process evaluation, they will be analyzed in relation to the outcome variables.
